### 3) Monitoring

Participants will be asked to monitor their adherence with exercise using an exercise diary. They will also be given a heart rate monitors to use while exercising so that they are able to track their exercise intensity and document these in the diary. An online platform (REDCap) will send prompts to participants to complete questionnaires relating to the side effects of their BC treatment and/or side effects from exercise sessions to aid in modulation of their treatment program.

### 4) Prompts and nudges

The participant will be able to opt-in to either online or phone messages reminding them of the exercise plan on any given day with scheduled exercise. Participants will also be encouraged to consider 'restructuring their environment' to provide prompts or reminders to exercise (e.g. place hand weights near the television, place their exercise shoes by the front door, set alarms on their phone to remind them to go for a walk etc).

### 5) Optimisation of social support

Following randomisation, participants will be invited to nominate a key support person (family member, friend, other) for the period of the trial. The support person will be invited to attend the baseline assessment and one-on-one sessions. Information regarding the importance of exercise across cancer treatment and strategies to facilitate this will be shared with the key support person. The role of the support person will be discussed and agreed upon by participant and support person, guided by the treating clinician.

### 6) Access to additional online support

An online digital resource (Physitrack) will contain individual exercise program(s) individual behaviour change strategies to aid in the uptake of the exercise. This online resource is currently used as a standard exercise prescription tool in the physiotherapy department at RPH. In addition, it will contain links to resources and advice relevant to individuals with breast cancer including psychological/emotional support resources, diet and nutrition education and education regarding referral pathways into available allied health services at RPH. As Physitrack requires participant mobile and/or email details for log-in purposes and to send exercise programs, there will be a section in the participant consent form with a check box allowing participants to opt in to this resource.

### 7) Optimisation of behaviour change technique use

An online digital workshop will contain advice for participants on identifying and effectively using behaviour change techniques based on the Behaviour Change Taxonomy (Michie et al., 2013); for example, action planning, problem solving, and habit formation. Additional booster sessions (over phone or telehealth) will also be available to participants, if appropriate.

## Product Accountability Procedures

Physitrack is currently used by the RPH Physiotherapy department as a part of routine exercise prescription. This will be made available to all participants in the SMART program to aid exercise prescription and adherence tracking. REDCap is also currently used by RPH physiotherapy department.

## Trial Duration/Schedule

The trial will run over a three-year period, with recruitment commencing in early 2024. Each participant will provide informed consent, after which they will complete a baseline assessment. On completion of the baseline assessments, participants will be randomised to either the experimental or control group and complete a 16-week intervention phase. Thereafter, all participants will complete a suite of re-assessments, (i) mid-way through the intervention phase, (ii) on completion of the intervention phase and, (iii) 12 months following randomisation.

| Milestones                                                           | Timeline        |
|----------------------------------------------------------------------|-----------------|
| 1. Recruit study personnel                                           | July 2023       |
| 2. Complete draft study proposal                                     | November 2023   |
| 3. Submit to ethics/governance                                       | November 2023   |
| 4. Approval obtained from all relevant HREC / RGO                    | February 2024   |
| 5. Commence recruitment (recruitment target = 15 participants/month) | March 2024      |
| 6. Commence intervention                                             | March 2024      |
| 7. Last participant recruitment                                      | March 2026      |
| 8. Complete intervention                                             | July 2026       |
| 9. Complete post-intervention assessments                            | August 2026     |
| 10. Complete long term follow-up assessments                         | March 2027      |
| 11. Data cleaning, analysis and report writing                       | From March 2026 |
| 12. Final study publications and report complete                     | September 2027  |

## Trial Termination

We will establish a Data Safety Monitoring Board (DSMB) of experienced researchers (n = 3), who are independent to the study group. This DSMB will meet after the successful recruit of each block of 50 trial participants. Progress of the trial participants (and any adverse events) and the changes in the primary outcome will be discussed. The DSMB will inform the study team of any concerns that would warrant discontinuation of the trial.

## Data identification

Following informed consent, participants will be allocated a study number. This number will be used in lieu of any identifying information on any data exported from REDCap.

## 5 Source and Selection of Participants

### Source of Participants

Participants will be recruited from the outpatient clinics at RPH. Those who appear to meet the study criteria will be identified in the weekly multi-disciplinary Breast Clinic team meetings. A nurse practitioner and/or other BC staff will approach those who meet criteria to share information regarding the trial.

There are some patients who complete radiation treatment prior to being given their script for their hormone medication by the radiation oncologist. The radiation treatment is completed outside RPH as there are no radiation oncology services onsite. For those patients receiving radiation oncology at SCGH, first contact may be made by the treating radiation oncologist to share information regarding the trial. It is noted that although first contact may occur at SCGH, these potential participants sit under the RPH Breast Clinic umbrella, i.e. those who were identified in the weekly RPH multi-disciplinary breast clinic team meetings following breast surgery at RPH but require adjuvant radiation treatment.

Those who express an interest will be contacted by a member of the research team, who will discuss the study with the potential participant. Informed consent will be gained prior to participation in the study.

### Participant inclusion criteria

Adults will be eligible to participate if they meet the following criteria:

1. Adult with newly diagnosed breast cancer (within the last 6 months)
2. Consent to treatment for their BC, which may include chemotherapy and/or endocrine therapy

### Participant exclusion criteria

Adults will be not eligible to participate if they meet any of the following criteria:

1. Cognitive impairment which limits ability to complete assessments and/or adhere to an independent exercise regime;
2. Unable to access internet/phone application;
3. Living in supported residential care;
4. Any co-morbid condition where exercise is contra-indicated (as determined by the treating specialist).

### Participant withdrawal criteria

(i.e. terminating investigational product/trial treatment) and procedures specifying:

*(a) when and how to withdraw participants from the project;*

Participants can ask to withdraw from this study at any time. To do so, they need to inform a member of the research team that no longer want to be involved. Contact details of the research team will be provided in the Participant Information Form. Withdrawal from the study would not mean a withdrawal of treatment. i.e., participants can still access usual care and no impact on any future BC treatment.

*(b) the type and timing of the data to be collected for withdrawn participant(s);*

We will ask any participant who chooses to withdraw from the study if we can retain any data already collected.

*(c) whether and how participants are to be replaced; and*

We will continue to recruit until the required sample size has completed the 16-week intervention period.

*(d) the follow-up for participants withdrawn from the project.*

Nil – other than usual care.

## 6 Treatment of Participants

### Description and justification for treatments, interventions or methods to be utilised

Those randomised to the experimental group will receive the *SMART* exercise program, as discussed above. Those randomised to the control group will receive usual care. This comprises education regarding the importance of exercise during cancer treatment, a pamphlet/information regarding appropriate off-site exercise groups. Separate oncology physiotherapy provision for patients undergoing chemotherapy treatment involves education strategies and the option to attend a weekly exercise session in the physiotherapy gym. However, exercise intervention as part of routine physiotherapy care for this patient group at RPH is currently through an “opt-in” system and resultant uptake of this service is low. In addition, the control group will receive a phone call from the research team once a month. During this phone call, information regarding healthcare utilisation will be collected and participants will receive generic encouragement to stay active during over the 16-week period.

The trial will run over a three-year period, with recruitment commencing in early 2024. Each participant will provide informed consent, after which they will complete a baseline assessment. On completion of these baseline assessments, participants will be randomised to either the experimental or control group and complete a 16-week intervention phase. Thereafter, all participants will complete a suite of re-assessments, (i) mid-way through the intervention phase, (ii) on completion of the intervention phase and, (iii) 12 months following randomisation.

### Permitted medications/treatments

This trial will not impact medication use. There are no inclusion/exclusion criteria based on medications.

## 7 Assessment of Efficacy

After recruitment, all study participants will complete an initial assessment to establish their baseline measures. The participants will be requested to complete the EORTC C30 questionnaire, as well as the breast cancer specific BR45 module, the EQ-5D-5L quality of life questionnaires and questionnaires measuring psychological determinants of behaviour change. The trial physiotherapist will also assess participant muscle strength (grip strength, upper limb and lower limb muscle strength) and exercise tolerance (6-minute walking distance). Participant body composition will also be measured using the SOZO analyser. These outcomes are discussed in detail below. This assessment will be repeated at the end of the intervention.

### PRIMARY OUTCOMES

**Health-related quality of life** will be measured using the EQ-5D-5L questionnaire and the EORTC Quality of Life C30 questionnaire together with the breast cancer specific BR45 module. These questionnaires have been validated for use in the BC population (Montagnese et al, 2021).

### SECONDARY OUTCOMES

**Peripheral muscle force-generating capacity** will be measured as; (i) grip strength, (ii) force generated during a maximum voluntary isometric contraction of the middle deltoids, biceps brachii and quadriceps femoris. These are described below.

*Grip strength* will be measured using a Jamar hand-held dynamometer (Surgical Synergies, SI Instruments, SA, Australia). The participant will perform the test in sitting. Starting position will be shoulder in adduction, elbow flexion to 90 degrees, forearm and wrist in neutral position. The participant will be encouraged to perform a maximal squeeze of the dynamometer for ~3 seconds. The test will be repeated 5 times (on each hand) and the measure that is the highest, but within 10% of one other will be recorded as the test result (Gittings, et al, 2018).

*Middle deltoids and biceps brachii strength* will be assessed using a Lafayette Muscle Meter no. 01165 (SI Instruments, SA, Australia). The participant will perform the test in sitting. Starting

position will be shoulder in adduction and neutral external rotation, elbow flexion to 90 degrees, forearm and wrist in neutral position. The participant will be encouraged to abduct their shoulder (for middle deltoids) or flex their elbow (for biceps brachii) with as much force as possible against the dynamometer for 3 seconds. The test will be repeated 5 times (on each arm) and the measure that is the highest, but within 10% of one other will be recorded as the test result (Gittings, et al, 2018).

*Quadriceps femoris strength* will be measured using a Lafayette Muscle Meter no. 01165 (SI Instruments, SA, Australia). The participant will perform the test in sitting. Starting position will be hip and knee flexion to 90 degrees. The participant will be encouraged to extend their knee with as much force as possible against the dynamometer for 3 seconds. The muscle meter will be stabilised with by the assessing therapist with the use of a nylon belt secured to the back leg of the chair, in order to maximise reliability. The test will be repeated 5 times (on each leg) and the measure that is the highest, but within 10% of one other will be recorded as the test result (Gittings, et al, 2018).

**Exercise tolerance** will be measured as the six-minute walk test (Schmidt 2013). This test will be performed according to standard guidelines (Schmidt 2013). The outcome measured is the distance walked in 6 minutes (6MWD). Each participant will perform the test twice and the longest 6MWD will be recorded as the test result.

**Muscle mass** and body composition will be measured via bioimpedance spectroscopy. This is a non-invasive measure of body composition performed using the SOZO analyser (Impedimed, Brisbane, Queensland). The test takes under a minute, with the participant clothed and standing on the testing platform. The SOZO device is already used in standard care in patient with BC to identify the presence of lymphoedema. This device applies 256 discrete current frequencies through the body, which provides estimates of tissue composition (skeletal muscle mass, fat mass, fat free mass), fluid variables (total body water, extracellular fluid and intracellular fluid), and a metabolic report (cell health, basal metabolic rate and active tissue mass) (Kyle, et al, 2004; Grisbrook, et al, 2015).

**Chemotherapy completion rates** will be extracted from medical records and recorded as a mean relative dose intensity (RDI), which records the actual chemotherapy medication dose intensity as a fraction of the original planned dose intensity, accounting for both the dose and the number of weeks in the chemotherapy cycle (Longo 1991). Any dose adjustments or dose delays will be obtained from the medical records and/or the treating oncologist and the percent of participants requiring dose adjustments or delay will be recorded.

**Psychological determinants of behaviour change** will be measured using; (i) the Capability, Opportunity, Motivation – Behaviour (COM-B; Michie et al. 2011) model factors, (ii) impairment in functioning, (iii) intention, (iv) self-efficacy, (v) habit. These are described below:

*COM-B framework factors* will be measured using the COM questionnaire (Keyworth et al., 2020). The COM questionnaire is a questionnaire measuring people's perceptions of each component of the COM-B model on their performance of target behaviours (Michie et al. 2011): physical and psychological capability; physical and social opportunity; and reflective and automatic motivation. The questionnaire was designed to be adaptable to different behaviours and populations, including exercise engagement (Keyworth et al., 2020). The measure has been adapted for the current study to assess participants' perceived ability to achieve their exercise goals; for example, "*I have the **PHYSICAL** opportunity to achieve my weekly exercise goals (e.g., time, the necessary equipment, space)*".

*Impairment in functioning* will be measured using the Work and Social Adjustment Scale (WSAS; Mundt et al., 2002). The WSAS is a questionnaire measuring the impact of someone's mental health on their ability to perform day-to-day functions, such as managing their home or engaging in leisure activities. The WSAS has demonstrated good validity in previous uses in the BC population (Lyons et al., 2015; Thandi et al., 2017).

*Intention to exercise* will be measured using two questions based on the theory of planned behaviour (Ajzen, 1991). The items will measure intention to perform aerobic exercise and resistance exercise with examples of each. Previous studies suggest that a single item per behaviour is sufficient to measure intention due to high correlations between items in lengthier measures, with the added benefit of reducing participant burden (Charlesworth et al., 2021; McAlpine & Mullan, 2022).

*Self-efficacy* will be measured using the Brief Self-Control Scale (BSCS; Tangney et al., 2004) and the Barrier and Task Self-Efficacy Scale (BTSES; Rogers et al., 2006). The BSCS is a validated questionnaire measuring general self-control that has often been used in studies exploring behaviour change (Allom et al., 2018). The BTSES is a questionnaire measuring self-efficacy around physical exercise developed to be used with the BC population and has shown good validity (Rogers et al., 2006).

*Habit* will be measured using the Habitual Tendencies Questionnaire (HTQ; Ramakrishnan et al., 2022) and the Self-Report Behavioural Automaticity Index (SRBAI; Gardner et al., 2012). The HTQ measures people's tendencies to rely on habits and has shown good validity when compared to similar measures such as the Routine subscale of the Creature of Habit Scale (Ersche et al., 2017; Ramakrishnan et al., 2022). The SRBAI measures people's perceptions of how automatic they find a specific behaviour, and has shown good validity when adapted to assess habitual physical exercise engagement (Phillips & Gardner, 2016; Weyland et al., 2022).

**Mood** will be measured using the Positive and Negative Affect Scale (PANAS; Watson 1988) questionnaire. The PANAS is a 20-item questionnaire of positive and negative mood that has been commonly used in the BC population, demonstrating high validity (Moreno et al., 2016; Voogt et al., 2005).

## OTHER VARIABLES

**Descriptive variables** will be recorded such as age, sex, body mass index, employment status, co-morbid conditions, stage of cancer and details of cancer treatment.

**Healthcare utilisation and adherence with exercise** will be assessed in both groups. In the control group, this will be documented during the monthly phone calls and exercise diaries. In the experimental group, this will be monitored by asking each participant during the weekly supervised sessions and also using exercise diaries (see Section 4, Monitoring). Regarding healthcare utilisation, we will ask each participant to recall the number of; (i) visits to the Emergency Department, (ii) inpatient admission days, (ii) outpatient appointments and, (iii) visits to any other healthcare provider (Y/N, who, number of visits). Regarding adherence with exercise, we will ask each participant to recall the number of minutes spent engaging in moderate or vigorous intensity exercise and details regarding any resistance exercise.

**Absenteeism and presenteeism** will be assessed using the iMTA productivity cost questionnaire (Bouwman 2015).

**Global rating of change** will be assessed by asking participants, on completion of the SMART exercise program, to indicate if their health-related quality of life or exercise tolerance had 'improved', 'worsened' or 'stayed the same'. Those participants who rated their walking ability as 'improved' or 'worsened' will then be asked to rate the degree of change on a seven-point scale (1 a little better to 7 a great deal better).

**Feasibility and acceptability** will be measured using; (i) Quantitative data from an acceptability and feasibility questionnaire, and (ii) qualitative data from exit interviews. These are described below:

*Quantitative data* will be collected using a questionnaire asking participants to rate their perceptions of the SMART exercise program (e.g., "*I thought the SMART exercise program was easy to understand*"). Participants can rate each item on a five-point scale (1 "*I don't agree at all*" to 5 "*I totally agree*"). Four open-ended items at the end of this questionnaire allow participants to include additional feedback (e.g., "*What did you like about the SMART exercise program?*").

*Qualitative data* will be collected using exit interviews upon completion of the SMART exercise program. Participants will have the opportunity to opt-in to semi-structured interviews to share more in-depth information about their experience with the SMART exercise program. Interviews will be conducted online and recorded using Teams, and are expected to last 30-45 minutes. Informed consent will be obtained from participants prior to the meeting and again before the interview or recording begins.

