## **Intervention**

A randomised controlled trial will be conducted. The experimental group will receive the *SMART* exercise program. To optimise adherence, participants in the *SMART* exercise program will be offered weekly one-on-one sessions with a senior physiotherapist for exercise prescription, monitoring or exercise uptake and potential treatment side effects, and to facilitate behaviour change. The target behaviour of the *SMART* program is to assist participants to build up to or maintain 150 minutes per week of moderate intensity aerobic exercise (or 75 minutes per week of vigorous intensity exercise) as well as two resistance training sessions per week. This target has been informed by the 2019 American College of Sports Medicine (ACSM) guidelines for exercise and cancer. Specific details of the *SMART* program have been described in Section 4 (under Intervention / Product Description).

The principles underpinning the *SMART* exercise program are that it will be:

**Self-determined:** Participants will be in the driver's seat regarding the establishment of weekly goals. They can choose to engage in exercises they enjoy (walking, swimming, cycling, dance etc) at the time of day that suits them best. Due to expected variation in baseline fitness levels and exercise preferences, the program will be individualised to each participant.

**Monitored:** The monitoring of adherence and treatment fidelity will occur through exercise diaries, monitoring of heart rate during the supervised and unsupervised exercise sessions and regular questionnaire data to monitor potential side effects relating to BC treatment and exercise.

**Adaptable:** The participant can choose the days/times they want to exercise and whether the weekly (supervised) session is completed at RPH, or via telehealth. In addition, participants will be briefed to periodise exercise routines according to potential BC treatment side effects (e.g. fatigue, pain, nausea) reported used the above monitoring strategies. Specifically, exercise programs will be adapted if the participant reports any symptoms (e.g. if an individual reports post-exertional malaise for 24 hours following an exercise program and their heart rate reached 140bpm/80% of their predicted HR max, they will be instructed to reduce their heart rate intensity to 110bpm/60% of their predicted HR max for their next exercise session).

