**Rehabilitation:** The target behaviour to work towards participation in 150 minutes moderate intensity aerobic exercise per week as well as two resistance sessions, as per the above ACSM guidelines.

**Telehealth supported:** A physiotherapist will offer supervised weekly sessions with each participant via telehealth (or in person at RPH) to supervise exercises, adjust their programs as needed and to implement behaviour change strategies to aid uptake of optimal exercise habits throughout their BC treatment. Participants will also receive email or phone prompts to complete their program on days according to their exercise routine.

Those randomised to the control group will receive usual care. This comprises education regarding the importance of exercise during cancer treatment, a pamphlet and information regarding appropriate off-site exercise groups. In addition, the control group will receive a phone call from the research team once a month. During this phone call, information regarding healthcare utilisation will be collected and participants will receive generic encouragement to stay active during over the 16-week period. The phone call in the control group is important to reduce the potential confounding effect of increased contact (attention) with healthcare professionals in the experimental group.

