- What is the health care utilisation, absenteeism and presenteeism over the 12 months following randomisation?

This is an exploratory question and data will be described using mean and standard deviation.

*The third secondary research question is:*

- Does performance on tests of peripheral muscle force-generating capacity and exercise tolerance, change with test repetition (i.e. is there a learning effect)?

This will be assessed using one-way repeated measures analysis of variance (ANOVA). That is, for each participant, data collected over consecutive trials (5 attempts for each measure of muscle force and 2 attempts for the 6MWT) compared to explore if there is an effect of test repetition on these outcomes.

*The fourth secondary research question is:*

What is the minimal detectable difference in health-related quality of life and exercise tolerance?

This will be assessed using anchor-based approach via a Receiver Operating Characteristic curve. This curve will determine the optimal operating point to discriminate between participants who rate themselves as changed vs unchanged at the end of the SMART program.

*The fifth secondary research question is:*

Do psychological determinants of behavioural change, such as capability, opportunity, and motivation affect adherence to the SMART program and physical activity maintenance?

This will be assessed using correlations and a Multiple Regression Analysis of the data from psychological determinant measures (COM-B factors, impairment in functioning, intention, self-efficacy, habit, and mood) across all time-points for each participant. Data from the exit interviews will also be analysed using qualitative methods (such as thematic analysis) to explore participants' reasons for engagement (or lack of engagement).

*The sixth secondary research question is:*

Does the SMART program improve mood, and does mood influence adherence to the program and physical activity maintenance?

This will be assessed using correlations between mood data from the PANAS (across all timepoints) and physical activity engagement.

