**1) What are likely to be the most important findings?**

- The effect of the SMART program on a range of patient centred outcome measures.
- The minimal detectable difference for measures of health-related quality of life and exercise tolerance in this patient population.
- Information regarding optimisation of measures of muscle force and exercise tolerance.
- Descriptive data on absenteeism and presenteeism.
- The effects of individual differences in psychological determinants of behaviour change (COM-B factors, impairment in functioning, intention, self-efficacy, habit, and mood) on physical adherence and maintenance.

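### Read literally, the global rating of change is tied to finishing SMART, so controls would supply no anchor for secondary question 4, although they have the same change scores

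*Protocol*

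**What the plan says.** On the global rating of change, Section 7 (Other Variables) states that it "will be assessed by asking participants, on completion of the SMART exercise program, to indicate if their health-related quality of life or exercise tolerance" (the three answers are better, worse or no different).

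Section 9 (Statistics and Interim Analysis, fourth secondary question) describes the analysis: "This will be assessed using anchor-based approach via a Receiver Operating Characteristic curve". The curve is to separate participants "who rate themselves as changed vs unchanged at the end of the SMART program".

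Section 2 (Intervention) fixes who has a SMART program to complete: "The experimental group will receive the *SMART* exercise program", whereas "Those randomised to the control group will receive usual care".

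The scores to be anchored are collected in both arms. Section 7 says "all study participants will complete an initial assessment to establish their baseline measures" and repeats that assessment at the end of the intervention. Section 4 (Trial Duration/Schedule) has every participant re-assessed at that point. The timing table in Section 7 (Efficacy assessment) lists HRQoL and the six-minute walk test before randomisation and at the end of the intervention phase. It has no row for the global rating.

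Section 15 names among the likely most important findings: "The minimal detectable difference for measures of health-related quality of life and exercise tolerance in this patient population".

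**The concern.** An anchor-based threshold needs two things from each person: a change score and a rating of perceived change. Controls will have the first. If the text is followed as it stands, they will not have the second, because they have no SMART program to finish.

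Two things are at stake. One is precision, since with 1:1 allocation half of the available paired scores cannot be used. The other is representativeness. Section 3 defines the study population for all research questions as newly diagnosed adults treated through the clinic, and Section 15 claims the threshold for that population. The estimate would come only from people who knew they had received a coached program and, if completion is taken strictly, had finished it.

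A later analysis plan cannot repair this. A rating of perceived change that is not asked at week 16 cannot validly be recovered afterwards.

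**Working it through.** **Who would be asked: the passages side by side**

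- Other Variables and the analysis section both name the SMART program, not the intervention phase.
- The timing table labels the week-16 column by the intervention phase, which applies to both arms. The rating has no row, so nothing there extends it to controls.
- For healthcare utilisation and exercise adherence, Other Variables says expressly that both groups are assessed.
- The exit interviews, which only SMART recipients can answer, are also timed to completion of the SMART program.

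The literal reading is therefore the SMART arm only, but it is an inference.

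**The protocol's own numbers.** Inputs from Section 9: difference 8, SD 20.52, α = 0.05 (taken as two-sided), power 0.80, drop-out 20%.

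- n per arm = 2 × [20.52 × (1.960 + 0.842) / 8]² = 103.3, rounded up to 104. This matches the protocol.
- 104 / 0.8 = 130 per arm, 260 in total. This also matches.

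The protocol gives no figure for the anchor analysis.

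**Size of the anchor sample**

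- SMART arm only: 130 randomised, about 104 evaluable.
- Both arms: 260 randomised, about 208 evaluable.
- Ratio 104 / 208 = 50%, or less if those who stop SMART early are not asked.

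**Precision of the AUC.** The Hanley-McNeil formula is SE² = [A(1−A) + (n₁−1)(Q₁−A²) + (n₂−1)(Q₂−A²)] / (n₁n₂), with Q₁ = A/(2−A) and Q₂ = 2A²/(1+A). The AUC and the share rating themselves changed are assumptions.

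- At A = 0.70 with half changed, Q₁ = 0.538, Q₂ = 0.576 and A² = 0.49.
- n = 104 (52 + 52): SE = 0.051, 95% half-width 0.100.
- n = 208 (104 + 104): SE = 0.036, 95% half-width 0.071.
- Over AUC 0.65 to 0.80 and 30 to 70% changed, the half-width is 0.085 to 0.120 at n = 104 and 0.060 to 0.084 at n = 208.
- The ratio stays near √2 = 1.41 throughout.
- Sensitivity 0.80 with half changed: 1.96 × √(0.8 × 0.2 / 52) = 0.109, against 1.96 × √(0.8 × 0.2 / 104) = 0.077.

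**Precision of the cut-off.** This comes from 3,000 simulated trials, all inputs assumed: 40/20/40% improved/worsened/unchanged, mean change +12/−12/0, SD 15, comparing improved with unchanged.

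| | n = 104 | n = 208 |
|---|---|---|
| SD of AUC | 0.056 | 0.039 |
| SD of Youden cut-off (points) | 6.2 | 5.1 |

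The formula above gives much the same AUC precision. The implied AUC is Φ(12 / (15√2)) = 0.714. With 41.6 per group (40% of 104) the SE is 0.056, and with 83.2 per group (40% of 208) it is 0.040.

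**Effect of a thinner unchanged group.** With a SMART-arm mix of 60/10/30 at n = 104, the SD of the AUC is 0.056 against 0.055 for the 40/20/40 mix in the same run. The SD of the cut-off is 6.0 against 6.2. A skew of this size barely affects precision for improved versus unchanged.

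**The case against.** The strongest reply is that the protocol nowhere says controls are not asked. The trial itself carries the SMART name, Section 3 defines one study population for all research questions, and question 4 is not limited to an arm. The end of the program may simply be shorthand for the end of the 16-week phase. The missing table row says nothing about arm either, because it leaves the rating unscheduled for SMART participants too. This stands: a reader might infer that the protocol deliberately discards half the data, and the text does not establish that.

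A one-arm anchor analysis is also valid in itself, and the relation between rating and score change could differ between arms, so pooling needs a check. The gain in the cut-off is modest. Even with both arms it would be uncertain by about 1.96 × 5.1 = 10 points, against 1.96 × 6.2 = 12 points for SMART alone. The simulation also drops the worsened group, whereas the plan contrasts changed with unchanged, and it was run with one set of means and SD.

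A reader might further infer that SMART ratings lean toward improved, or that too few people will be unchanged or worsened. Neither is shown. The skewed mix hardly altered precision for the contrast tested, and no threshold for worsening was calculated.

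What remains is that two passages agree on SMART-specific wording, a neighbouring item states both groups expressly, and nothing in the timing table corrects the literal reading. Anyone building the data-collection forms from this text could leave controls out.

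**Conclusion.** The point holds as a wording and data-collection gap of minor severity. On the literal reading, secondary question 4 would use about 104 of 208 evaluable participants, all from the arm that knew it received SMART, and AUC intervals would be about 1.4 times wider than with both arms. The halving follows from the protocol's allocation and sample size. The AUC values, rating shares and simulation inputs are illustrative assumptions.

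The threshold may also fail to represent the population for which Section 15 claims it, though the direction and size of any bias are unknown. The documents do not support saying that controls are expressly excluded or that the ratings will be biased. The primary comparison and the sample size are unaffected.

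**What to change.** - In Other Variables, state that all randomised participants in both arms are asked the global rating at the end of the 16-week intervention phase, whether or not they finished SMART. Word it as change since the baseline assessment.
- Add a row for the rating to the timing table, under completion of the intervention phase.
- Reword the fourth secondary question in Section 9 to the same time point and population.
- Run the anchor analysis on both arms, and check whether the relation between rating and score change differs by arm.

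The cost is one short question for controls at an assessment they already attend, with no extra visit or staff. If both arms were always intended, the text and table still need these corrections.
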